### **Blinding**

Due to the nature of the trial, it is not possible to have a completely blinded design. Participants will know which intervention they are receiving, and the group leaders and health visitors will also know which families are in the intervention arm. Interviewers and coders are blind to group allocation, but participants might reveal allocation status at T2 or T3 assessment. All participants are given an identification number to ensure that the researchers performing the analysis are blinded to allocation status.

### **Outcomes**

Data are collected at three time points: T1 (baseline), T2 (post-intervention, around four months after baseline), and T3 (follow-up, when the child is 18-months-old). Data collection takes place at the parent's home at each of the three time points. All interviewers are trained and experienced in carrying out interviews in participants' homes. The interviewer collects the main part of the background data (for example, education and work status), but the majority of the outcomes are self-reported on computer by the mother. If possible, the father or the partner also completes the questionnaire. Families are compensated by a 200 DKK (approximately 27€) gift card at each visit. The visits are expected to last between 40 minutes (T1) and an hour (T2 and T3). All data are kept at a secure server with password protection. A description of the trial outcomes are outlined below. The timing of the outcomes is shown in Table 1.

### **Primary outcomes**

#### ***Parenting***

**Karitane parenting confidence scale** The Karitane Parenting Confidence Scale (KPCS) [54, 55] measures parenting confidence for parents of infants aged 0 to 12-months-old. The KPCS consists of 15 items that are rated on a four-point scale (No, hardly ever, No, not very often, Yes, some of the time, Yes, most of the time). A Danish version of KPCS has been developed for the trial by the author and [name],

**Table 1** Timing of outcomes

|                                                                                                                                                          |                | T1 Baseline | T2 Post-test | T3 Follow-up |
|----------------------------------------------------------------------------------------------------------------------------------------------------------|----------------|-------------|--------------|--------------|
| Parent measures                                                                                                                                          |                |             |              |              |
| Karitane Parenting Confidence Scale                                                                                                                      | KPCS           | ✓           | ✓            |              |
| Parental Stress Scale                                                                                                                                    | PSS            |             | ✓            | ✓            |
| Major Depression Inventory                                                                                                                               | MDI10          | ✓           | ✓            | ✓            |
| World Health Organization Well-Being Index                                                                                                               | WHO-5          | ✓           | ✓            | ✓            |
| Rosenberg Self-Esteem Scale                                                                                                                              | RSS            |             | ✓            |              |
| Being a Mother                                                                                                                                           | BaM-13         |             |              | ✓            |
| Parental Reflective Functioning Questionnaire                                                                                                            | PRFQ-1         |             |              | ✓            |
| Parenting Sense of Competence                                                                                                                            | PSOC           |             |              | ✓            |
| Sense of Coherence                                                                                                                                       | SOC13          | ✓           |              |              |
| Background questions: age, education, occupation, ethnicity, number of children, household status, housing situation, household economy, substance abuse |                | ✓           | ✓            | ✓            |
| Single items on parent health, parent life satisfaction, support, and network.                                                                           |                | ✓           | ✓            | ✓            |
| Child measures                                                                                                                                           |                |             |              |              |
| Ages and Stages Questionnaire - Social-Emotional                                                                                                         | ASQ-SE         | ✓           | ✓            | ✓            |
| Strengths and Difficulties Questionnaire                                                                                                                 | SDQ            |             |              | ✓            |
| Cognitive Development Questionnaire                                                                                                                      | CDQ            |             |              | ✓            |
| Single items on child health and child temperament                                                                                                       |                | ✓           | ✓            | ✓            |
| Parent-child measures                                                                                                                                    |                |             |              |              |
| Mother and Baby Interaction Scale                                                                                                                        | MABISC         |             | ✓            |              |
| Video (15 minutes)                                                                                                                                       | EAS/CARE-Index |             | ✓            |              |
| Single items on interactions with child                                                                                                                  |                |             | ✓            | ✓            |

and is administered at T1 and T2, but not at T3 since the child is too old at this time.

**Parenting stress scale** The Parenting Stress Scale (PSS) [56] measures parenting stress and can be used with parents of children up to 18-years-old. The PSS consists of 18 items that are rated on a five-point scale (Strongly disagree, Disagree, Undecided, Agree, Strongly agree). A Danish version of the PSS developed by the author and [name] is administered at T2 and T3, but not at T1 since the items are not considered relevant for parents of newborns.

**Parenting sense of competence scale** The Parenting Sense of Competence Scale (PSOC) [62, 63] measures how parents perceive their own competences as a parent. The PSOC consists of 16 items and two subscales: efficacy and satisfaction. The PSOC is scored on a six-point Likert scale (Strongly Agree, Somewhat Agree, Agree, Disagree, Somewhat Disagree, Strongly Disagree). A Danish version of the PSOC developed by [name] and [name] is administered at T3.

**Sense of coherence** –The Sense of Coherence (SOC13) [64] measures how people manage stress and stay well within the salutogenic framework phrased by Antonovsky [65]. The SOC13 consists of 13 items that are scored on a five-point Likert scale (Never, Rarely, Occasionally, Often, Always). A Danish version of the SOC13 developed by [name] is administered at T1.

**Single items** Single items on parent health, parent life satisfaction, support, and network are administered at T1, T2, and T3. Items are scored on an 11-point scale, with 0 representing Worst possible health/Disagree completely/Often and 10 representing Best possible health/Agree completely/Never.

### Children

**Ages and stages questionnaire - social-emotional** The Ages and Stages Questionnaire - Social-Emotional (ASQ-SE) [31] measures social-emotional problems and competencies in children aged three months to five years. The ASQ-SE consists of 19 to 33 items that are rated by parents on a three-point scale (Often or always,

Sometimes, Rarely or never) and a box parents may check if the behavior is a concern for them. A Danish version based on the experimental version of a second edition of the ASQ-SE has been developed for the trial by the author and is administered at T1, T2, and T3, even though most of the infants will be less than three-months-old at T1.

**Strengths and difficulties questionnaire** –The Strengths and Difficulties Questionnaire (SDQ) [66–68] measures child behavior and psychopathology in children from 2 to 17-years-old. The SDQ consists of 25 items (five domains: hyperactivity/inattention, peer problems, conduct problems, emotional symptoms, and pro-social behaviors) that are rated by parents on a three-point scale (Not true, Somewhat true, Certainly true). The 2014 revision of the Danish two to four year version is administered at T3. The SDQ is used even though the children are 18-months-old and not 24 months as is the recommended lower age limit.

**Cognitive development questionnaire** The Cognitive Development Questionnaire (CDQ) [69] measures cognitive development of children from 8 to 24-months-old. The CDQ consists of two sections: section one with 19 scripted games for parents to play with their infant, and section two with 16 items asking about everyday behaviors. Items are rated by parents on a yes/no scale supplemented with information on how many blocks were used. A Danish version of the CDQ has been developed for the trial by the author and is administered at T3.

**Single items** Single items on child health, temperament, height, and weight are administered at T1, T2, and T3. Child health and temperament are scored on an 11-point scale with 0 representing Worst possible health/Disagree completely and 10 representing Best possible health/Agree completely.

### Relationship

**Mother and baby interaction scale** The Mother and Baby Interaction Scale (MABISC) [70, 71] measures the mother-infant relationship. The MABISC consists of 10 items that are scored on a five-point Likert scale (Always, Most of the time, Occasionally, Not often, Never). A Danish version of the MABISC has been developed for the trial by the author. The MABISC is administered at T2.

**Video** A 15-minute video of the mother and baby is recorded at T2 to assess the mother-infant relationship. The mother is instructed to be with her child on a mat on the floor and to interact with her child as she

normally would. The 15-minute video consists of the following phases: six minutes of free play, four minutes of frustration where the child is given a toy that is challenging, 30 seconds of separation, and three minutes of reunion. The videos will be coded within either the Emotional Availability Scales (EAS) system [72] or the Care Index system [73].

**Single items** Single items measuring parent/child interaction such as singing songs, dancing, and telling stories are administered at T2 and T3. Three single items are administered at T2. One is scored at an 11-point scale with 0 representing Disagree completely and 10 representing Agree completely, and the other two are scored by marking how many days a week the activity happened. At T3, 14 items are administered. These 14 items were adapted from the evaluation of the Preparing for Life program [74], and are scored on a six-point scale (More than once a day, About once a day, A few times a week, A few times a month, Rarely, Not at all).

### Background questions

Background questions and socio-demographics are collected at T1, T2, and T3. They measure parent age, education, occupation, ethnicity, number of children, household status, housing situation, household economy, substance abuse, child birth weight, child gestation at birth, and child health.

### Recruitment and participation

All levels of parent recruitment and participation will be examined. This includes recruitment procedures (information leaflets, YouTube video, challenges and barriers for the health visitors), consent rates, intervention uptake, and mother and father participation in the IYPB sessions. Parent satisfaction with the IYPB is measured by a questionnaire, and a qualitative study looking into how parents experience participation in the IYPB as a universal prevention will be performed.

### Implementation and treatment fidelity

During the trial, a qualitative study of the implementation of the IYPB in one of the municipalities will be performed to look into challenges and successes experienced when moving from using the IYPB as a targeted program to rolling it out as a universal intervention. Treatment fidelity is measured by session checklists completed by group leaders at the end of each session.

### Future outcomes

If further funding is obtained data will be collected at later time points (such as 36 and 48 months) to look for long term effects and dropout rates. In Denmark, researchers have access to very rich register data at a relatively low

cost on central long term outcomes, such as school performance, education, income, hospitalization, diagnoses, prescription drug use, marriage status, and childbirths. These are key outcomes, but they are usually not easily collected without the access to register data. Participants will be followed up on in central registers at Statistics Denmark at later time points (for example when the children are 20 and 30-years-old) to look for long term effects of the intervention on both parent and child outcomes (for example school performance, work status, and diagnoses). Register data can be collected for all participants and can be compared to the full population if needed.

### Data analysis

#### Sample size

Lancaster *et al.* [75] recommended that the sample size of a pilot study be a minimum of 30 participants to be able to estimate parameters. As a small effect size is expected with a universal sample, the size of the pilot trial is 128 mothers. With a sample size of 128, a power of 0.8, and a two-sided alpha level of 0.05, it is possible to detect an effect size of 0.50 (Cohen's *d*).

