### **Randomization**

An independent researcher computes a random allocation list stratified by municipality and with a block size of three. The allocation ratio is 2:1 (IYPB:UC), as it is important for the municipalities to have enough families in the IYPB intervention arm to start the groups. After the baseline assessment is completed, the interviewer informs a designated research

administrator that the interview has been completed. The research administrator then randomizes the family by adding the name to the randomization list in the order the names arrive from the interviewer. Then the contact person in the municipality is informed about the allocation status of the family. Participants are informed by their health visitor as to which arm of the study they have been allocated to. In the case where consent to treatment is withdrawn but the participant agrees to remain in the research study, the participant is followed to completion.

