#### Planned statistical analysis

Analyses are performed using the software packages R 3.2.1 and STATA 13, or later versions. The data analyst will be blinded to allocation arm. Analysis and presentation of data will be in accordance with the CONSORT guidelines, in particular the extensions to pragmatic trials [76] and nonpharmacologic interventions [77]. Standard descriptive statistics (means, medians, ranges, standard deviations, frequencies, and percentages) will be used to report demographics, and baseline and outcome scores. Data will be examined for missing data and multiple imputation strategies will be used if necessary. Missing data are, however, expected to be low as data are collected through home interviews and the families are compensated.

Primary and secondary outcomes will be analyzed using multiple regression for continuous outcomes, and logistic regression for binary outcomes controlling for baseline scores where possible. A two-tailed test  $\alpha = 0.05$  will be used and parameters will be summarized using 95 % confidence intervals. If assumptions for parametric analysis are not met, non-parametric tests like the Mann-Whitney *U* test will be used. To account for group or therapist effects, standard errors will be clustered around the group for the parents in the intervention arm.

Analysis will follow intention-to-treat (ITT) principles, but completer analysis (such as complier average causal effects (CACE) based on treatment received will also be performed. To examine how non-compliance affects results two levels of participation will be explored: parents that have participated in at least three of the eight

sessions, and parents that have participated in at least six of the eight sessions.

As larger effects are expected in parents who present difficulties at the time of recruitment, separate analysis will be carried out for the following three groups: parents who have baseline scores in the clinical range of the measures, parents who are scoring within the lowest 25 % of the distribution at baseline, parents who are scoring within the lowest 50 % of the distribution at baseline.

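### The stated 80% power for d = 0.50 with 128 mothers assumes equal allocation; under the trial's 2:1 allocation it is about 75% in an unadjusted comparison, before clustering and dropout

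*Protocol*

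**What the plan says.** The protocol's only sample-size statement is in the Sample size paragraph under Data analysis. It sets the size with "As a small effect size is expected with a universal sample, the size of the pilot trial is 128 mothers" and then states that, at that size, "a power of 0.8, and a two-sided alpha level of 0.05, it is possible to detect an effect size of 0.50" (Cohen's d). It mentions no allocation ratio, intracluster correlation (ICC), dropout rate or covariate adjustment.

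Other sections fix features that bear on the figure:

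- Randomization: "The allocation ratio is 2:1 (IYPB:UC"; the Abstract gives the same ratio.
- Intervention: the program is delivered in groups of six to eight parents.
- Planned statistical analysis: "standard errors will be clustered around the group for the parents in the intervention arm". Outcomes are adjusted for baseline scores where these exist, and little missing data is expected, though no rate is given.
- Primary outcomes and Table 1: the KPCS is measured at T1 and T2; the PSS is measured at T2 and T3 only.

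**The concern.** A total of 128 for d = 0.50, 80% power and two-sided alpha 0.05 is the familiar two-sample t-test answer for equal arms. The trial does not have equal arms. For a fixed total, unequal allocation raises the variance of the difference between means, so the stated power and the stated design cannot both hold for the calculation as described.

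The rationale also sits badly with the number. The paragraph supports 128 by an expected small effect and then names a detectable effect of 0.50, which is conventionally medium.

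This is an external pilot, so the stakes are limited, but they exist. The protocol chose to make a power claim and plans two-tailed tests at 0.05. A reader of a non-significant result would take the claim at face value, and the figure could be carried into planning the definitive trial.

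**Working it through.** **Inputs from the protocol.** N = 128, two-sided alpha 0.05, d = 0.50 and power 0.80 (Sample size); 2:1 allocation (Abstract, Randomization); groups of six to eight (Intervention). The ICC, the dropout rate and the baseline-outcome correlation r are not given, so every figure that uses them below is an assumption.

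**Method.** Two-sample t-test with noncentral t. Noncentrality δ = d × √(n₁n₂/(n₁+n₂)), with n₁+n₂−2 degrees of freedom. For N = 128 the critical value is 1.979 (126 df).

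**1. Reproduce the stated figure.** With 64 and 64: δ = 0.50 × √(4096/128) = 0.50 × √32 = 2.828, power 0.801. This matches the stated 0.80.

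**2. Apply the trial's allocation.** With 85 and 43: δ = 0.50 × √(3655/128) = 0.50 × √28.55 = 2.672, power 0.755. The effect detectable with 80% power is d = 0.528. The split 86:42 gives 0.750. The normal approximation gives 0.762, against 0.807 for 64:64, so the gap does not come from the choice of method. A one-sided test at 85:43 would give 0.844, but the protocol specifies two-sided.

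**3. Size needed at 2:1.** With 96 and 48: 4608/144 = 32, so δ is again 2.828 and power is 0.802. With 94 and 47 (141 in all) power is 0.794. The smallest exact 2:1 total is therefore 144.

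**4. Clustering and dropout (assumed values).** Divide the intervention-arm n by 1 + (m−1) × ICC with m = 7, and multiply both arms by (1 − dropout). For example, with ICC 0.05 the factor is 1.30, so 85/1.30 = 65.4 against 43. Power at d = 0.50:

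| ICC | No dropout | 5% | 10% | 15% |
|---|---|---|---|---|
| 0 | 0.755 | 0.733 | 0.710 | 0.685 |
| 0.01 | 0.747 | 0.725 | 0.701 | 0.676 |
| 0.05 | 0.713 | 0.691 | 0.667 | 0.642 |
| 0.10 | 0.675 | 0.652 | 0.628 | 0.603 |

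With no dropout and ICC 0.05, groups of 6 give 0.720 and groups of 8 give 0.707. If groups are taken to shrink with dropout, the loss is slightly smaller (0.674 rather than 0.667 at ICC 0.05 and 10%).

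**5. Baseline adjustment (assumed r).** Replace d by d/√(1−r²). At 85:43 without clustering or dropout:

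- r = 0.3 gives 0.794.
- r of about 0.32 gives 0.80, since 0.50/√(1−0.323²) = 0.528.
- r = 0.5 gives 0.865.

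With ICC 0.05 and 10% dropout as well, r = 0.5 gives 0.789. None of this applies to the PSS, which has no T1 score.

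**The case against.** **Baseline adjustment.** The strongest objection is that the analysis will adjust for baseline where it can, and that this may restore the power. This stands for the KPCS. A reader might infer from step 2 that 75% is the most the trial can have. The protocol does not support that: at 85:43 the KPCS reaches 80% with r of about 0.32, before clustering and dropout. But the Sample size paragraph does not invoke adjustment, that r offsets only the allocation loss, and the PSS gains nothing.

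**Assumed inputs.** A reader might take about 67% (ICC 0.05, 10% dropout) as the trial's true power. It is one cell of an assumed range. The protocol gives no ICC, expects little missing data and plans multiple imputation if needed. If partners count toward the six to eight parents, fewer mothers share a group and the clustering loss is smaller. Only the 2:1 shortfall follows from the protocol's own numbers.

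**Expected effect.** It is tempting to set d = 0.50 against the effects of 0.13 and 0.20 quoted in the Background and conclude that the trial is hopelessly underpowered for its own expectation. Those effects concern disruptive behavior in children aged three to nine, not parenting confidence or stress. The Background's one parenting-confidence figure for this program is 0.61, though that is a change over time in a small sample of mothers living in poverty. Neither is a sound benchmark here.

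**Small-effect wording.** The sentence can be read as explaining why the pilot exceeds the minimum of 30 cited just before it. That is a fair reading, but the wording still suggests that 128 suits a small effect.

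**Pilot status.** A definitive trial would be planned mainly from the pilot's estimates, and 95% confidence intervals are already promised. Both points lower the severity; neither makes the stated power correct.

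**Conclusion.** Wrong as written, of modest severity. The stated 80% belongs to a 64:64 trial. With the 2:1 allocation that the protocol fixes, an unadjusted comparison before clustering and dropout has 75.5% power for d = 0.50. That is about 4.5 percentage points below the stated 80%, or a detectable effect of 0.53 in place of 0.50. This conclusion uses only the protocol's own inputs and a two-sample t-test.

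Clustering in the intervention arm and dropout push the figure down, and baseline adjustment may push it up for the KPCS. The size of each depends on values the protocol does not give. The mismatch between an expected small effect and a detectable d of 0.50 is real but secondary.

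**What to change.** Keep 128 mothers and replace the power sentence with wording such as:

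> With about 85 IYPB and 43 UC mothers, the trial has about 75% power for d = 0.50 (80% power for d = 0.53) in an unadjusted comparison, before allowing for group clustering and dropout.

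Then add two statements:

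- Clustering in the intervention arm and dropout lower this. Label any figures as assumptions and show a range: for example, groups of 7 with ICC 0.05 give about 0.71, and 10% dropout as well gives about 0.67.
- Baseline adjustment may raise power for the KPCS (r of about 0.32 offsets the 2:1 loss only) but not for the PSS, which has no baseline.

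Reword the small-effect justification: say that 128 exceeds the cited pilot minimum and that the trial is not powered for small effects.

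The cost is one paragraph and a slightly less favorable stated figure. No extra families are needed, and neither the allocation nor the planned analysis changes.

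### The stated detectable effect of d = 0.50 is the equal-allocation figure; at the trial's 2:1 ratio, 128 mothers give 75.5% power for it in an unadjusted comparison

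*Protocol*

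**What the plan says.** The Sample size section sets the total: "the size of the pilot trial is 128 mothers". It then gives the power statement for that total: "a power of 0.8, and a two-sided alpha level of 0.05, it is possible to detect an effect size of 0.50" on Cohen's scale. It mentions no allocation ratio, clustering, loss to follow-up or baseline correlation.

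Three other parts of the protocol bear on that figure:

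- **Randomization:** "The allocation ratio is 2:1 (IYPB:UC"). The reason given is operational: the municipalities need enough intervention families to start groups.
- **Intervention:** the programme is delivered in groups of six to eight parents.
- **Planned statistical analysis:** "standard errors will be clustered around the group for the parents in the intervention arm". The same section plans regression that adjusts for baseline scores where it can, and it expects little missing data.

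The two primary measures differ in what is available at baseline. Table 1 lists the Karitane Parenting Confidence Scale (KPCS) at T1 and T2. It lists the parental stress scale (PSS) at T2 and T3 only.

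**The concern.** A total of 128 with 80% power, two-sided 0.05 and d = 0.50 is the familiar result for a two-sample t-test with 64 in each arm. This trial does not have 64 in each arm. For a fixed total, unequal allocation raises the standard error of the difference, so the sentence credits the design with more power than an unadjusted comparison has.

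At stake is how the results are read. The protocol plans two-sided tests at 0.05 on both primary measures, and a reader of a null result will judge it against the stated power. The question here is only whether the number belongs to this design. Whether 0.50 is a suitable target, given that the same section says "As a small effect size is expected with a universal sample", is a separate matter.

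**Working it through.** **Inputs from the protocol:** total 128; two-sided alpha 0.05; power 0.80; d = 0.50 (so SD = 1); allocation 2:1, which is about 85 and 43; groups of six to eight parents in the intervention arm only.

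**Method:** two-sample t-test, with power from the noncentral t distribution. The standard error (SE) of the difference is sqrt(1/n1 + 1/n2), the noncentrality is d/SE, and the degrees of freedom are n1 + n2 − 2 = 126 (critical value 1.979).

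**1. Reproducing the stated figure (64:64).** SE = sqrt(1/64 + 1/64) = 0.1768. Noncentrality = 0.50/0.1768 = 2.828. Power = 80.1%, and the effect detectable with 80% power is 0.499. The stated figure is therefore the equal-allocation result.

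**2. The trial's own ratio (85:43).** SE = sqrt(1/85 + 1/43) = 0.1871. Noncentrality = 0.50/0.1871 = 2.672. Power = 75.5%, and the detectable effect is 0.528. Other conventions do not recover 80%: the normal approximation gives 76.2%, and a one-sided test gives 84.4%.

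**3. The total that 2:1 would need for the stated figure.** 1/96 + 1/48 = 3/96 = 1/32, the same as 1/64 + 1/64. So about 144 families (96:48) match the stated precision, with power 80.2%. That is 144/128 = 1.125, or 12.5% more.

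**4. Clustering (assumed values).** With m families per group, the intervention-arm variance is multiplied by DE = 1 + (m − 1) × ICC, so SE = sqrt(DE/85 + 1/43). The detectable effect is close to 2.823 × SE, where 2.823 = 0.528/0.1871. I assume m = 7; the protocol gives no ICC.

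| ICC | DE | SE | Power for d = 0.50 | Detectable d |
|---|---|---|---|---|
| 0.02 | 1.12 | 0.191 | 73.9% | 0.54 |
| 0.05 | 1.30 | 0.196 | 71.5% | 0.55 |
| 0.10 | 1.60 | 0.205 | 67.7% | 0.58 |

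**5. Clustering and 10% loss (both assumed).** The arms become 76.5 and 38.7. At ICC 0.02, SE = sqrt(1.12/76.5 + 1/38.7) = 0.201 and the detectable d is about 0.57. At ICC 0.10, SE = sqrt(1.60/76.5 + 1/38.7) = 0.216 and d is about 0.61.

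**6. Baseline adjustment (correlation assumed).** If r is the correlation of the baseline covariates with the outcome, the detectable effect is multiplied by sqrt(1 − r²). At r = 0.32 the factor is 0.947, and 0.528 × 0.947 = 0.50. So r of about 0.32 cancels the 2:1 loss alone. With m = 7 and ICC 0.05, the r needed is sqrt(1 − (0.50/0.554)²) = 0.43.

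**The case against.** The strongest reply is that the planned analysis is not the unadjusted comparison. It adjusts for baseline where possible, and a T1–T2 correlation of only 0.32 for KPCS would restore d = 0.50 before clustering and loss. This stands as a limit on the conclusion. A reader might infer that the trial cannot reach 80% power for d = 0.50, but the documents do not support that: with no correlation given, the adjusted KPCS analysis could fall on either side of 80%. It does not rescue the sentence, which neither invokes adjustment nor states a correlation.

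A reader might also infer that nothing can offset the loss for PSS, because it has no T1 score. That goes too far. The adjustment is not confined to the same scale, and Table 1 lists KPCS, the depression inventory (MDI10), WHO-5 and SOC13 at T1. Any gain for PSS depends on how well those predict it, which is unknown.

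The clustering and loss figures are also open to challenge, and fairly so:

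- The ICC is assumed.
- The protocol counts parents per group, not families. With 4 mothers per group and ICC 0.05, power is 73.5% and the detectable d is 0.54.
- The protocol expects missing data to be low, gives reasons and provides for multiple imputation. Leaving out attrition is a planning choice, not an arithmetic error.

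Finally, this is an external pilot with several aims besides estimating effects, and its 95% confidence intervals will show the precision achieved. A reader might infer that a definitive trial would be sized from the wrong figure. The protocol says only that the pilot will establish parameters for such a trial, so that does not follow. These points limit the consequence; they do not make the number right.

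**Conclusion.** The stated figure is wrong for the design as written. It is the 64:64 result, and nothing else in the protocol corrects it. From the protocol's own numbers alone, the 2:1 ratio lowers unadjusted power for d = 0.50 from 80.1% to 75.5% (4.6 points) and raises the 80% detectable effect from 0.50 to about 0.53.

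Clustering in the intervention arm lowers power further for any positive ICC. That direction is certain, but the amounts (0.54 to 0.58, or 0.57 to 0.61 with 10% loss) rest on an assumed ICC of 0.02 to 0.10, 7 families per group and the assumed loss. Baseline adjustment pulls the other way by an amount the protocol does not allow one to calculate.

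The severity is moderate: a misstated figure that wording can correct. It does not show that the sample size or the allocation ratio has to change.

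**What to change.** Keep 128 mothers and the 2:1 ratio, and replace the power sentence in the Sample size section with one to this effect:

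> 128 mothers randomised 2:1 (about 85:43) give 80% power at two-sided 0.05 to detect d = 0.53, or 75.5% power for d = 0.50, before group clustering, loss to follow-up and baseline adjustment.

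Then add a short illustration, with its values marked as assumptions:

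- About 7 families per group and an ICC of 0.02 to 0.10 raise the detectable d to about 0.54–0.58, or about 0.57–0.61 if 10% are also lost.
- Baseline adjustment multiplies the detectable d by sqrt(1 − r²), where r is the correlation of the baseline covariates with the outcome. An r of about 0.32 offsets the 2:1 loss alone.
- PSS has no T1 score of its own, so any gain there depends on other baseline measures.

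The cost is a few sentences and a slightly less favourable stated figure. No extra families are needed, and randomisation, outcomes and tests stay as they are.
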